#### Second step

Based on the result of the respiratory polygraphy, the lesion diameter confirmed on the MRI at day 1, and after the study physician has checked the remaining exclusion criteria listed in Table 1, eligible patients with significant SDB (AHI > 20/h) are randomized to ASV treatment (SDB ASV+) versus no ventilation treatment (SDB ASV−) applied between the 2nd and 89th night following stroke. Eligible patients with an AHI < 5/h can be included into the control cohort without SDB (noSDB group). Figure 1 gives an overview on the study design.

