### Assessment of outcomes

#### Primary outcome: final infarct change from visit 1 to visit 6 on magnetic resonance imaging (MRI)

The infarct volumes (measured in cm^3^) are assessed at visit 1 and visit 6 (see Table 2 displaying which assessments are performed at which visits, according to [27]). We measure infarct volume on DWI (diffusion weighted imaging) MRI scans at visit 1, i.e. after potential lysis therapy and before ASV-treatment, and on T2w MRI scans at visit 6 (see Fig. 2 for illustration). Two independent raters blinded regarding patients’ treatment allocation and presence of SDB assess the primary MRI outcome supervised by two senior neuroradiologists. Change of lesion volume from visit 1 to visit 6 is compared between the treatment groups (SDB ASV+ and SDB ASV−). Change of lesion volume from visit 1 to visit 6 will also be compared between the patient groups with sleep-disordered breathing (SDB ASV+ and ASV− together) and without sleep-disordered breathing (noSDB).

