##### Assessment of stroke severity and clinical outcome

Stroke severity is assessed by means of the NIHSS at admission (visit 0), after 24 h (visit 1), at patient’s hospital dismissal (visit 4) and at the 90 ± 7 days’ follow-up during visit 6.Modified Rankin Scale (mRS) [29] is used to characterize patient’s (in)dependence in daily functioning and in performance of daily activities before the stroke and will be assessed before hospital discharge (between visits 1 and 4).Clinical stroke outcomes are assessed at visit 6 and visit 7 using the Barthel Index (BI) [30] and the mRS [29] as well as patient’s subjective rating about quality of life (EQ-5D-3L) [31].Sensorimotor upper extremity functions are assessed by the Fugl-Meyer Assessment of upper extremities, which has provided to be reliable and sensitive to assess upper-extremity recovery following stroke at 4 to 7 days after stroke and at 3-month follow-up (visit 4 and 6) [32, 33].Death and new cardio-/cerebrovascular events: a composite endpoint of death from any cause, stroke, transient ischaemic attack (TIA), nonfatal myocardial infarction, unplanned hospitalization (or unplanned prolongation of a planned hospitalization) for heart failure or unplanned hospitalization (or unplanned prolongation of a planned hospitalization) leading to urgent revascularization is assessed at visit 4, visit 6, and visit 7 (see Additional file, table 1 for a definition of the events)Cognitive outcomes: Cognitive performance measures, assessed by neuropsychological tests (see Additional file, table 2 for details) of language, neglect, attention, executive functions and verbal and visual short-and long-term memory, are obtained at visit 4 and visit 6.

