### Statistical analysis

Descriptive summary statistics for efficacy and safety variables will be presented for the entire population and by study arm (no SDB patients, and SDB patients randomized to the ASV+ and ASV- arms). Inferential statistical methods will be used to highlight interesting aspects of the data and primarily for the comparison of outcome variables in the two randomized arms. In addition, comparisons of selected outcomes will be carried out between the two cohorts. The significance level of all statistical tests will be 5% and no control for multiplicity will be applied. Corresponding 95% confidence intervals will be presented as appropriate.

Two main analysis populations will be used:
*Full Analysis Set (FAS)*: this population will include all enrolled patients. In line with the intent-to-treat principle, randomized patients will be analysed according to the treatment group assigned at randomization. The FAS will be the main analysis population for efficacy and safety variables. In particular, it will be the primary population for the comparative analysis of the two randomized treatment groups.*Per-protocol (PP) population*: it will include randomized patients fulfilling all selection criteria and sufficiently compliant with the protocol. The list of criteria, leading to exclusion from the PP analysis, which, among other criteria, will consider the compliance with ASV procedures, will be finalized before database closure for the primary analysis.

The comparative analysis of infarct volume data will be performed using an analysis of covariance model with adjustments at least for the stratification variables used at randomization. In case of violation of the statistical validity conditions for the model, a suitable non-parametric alternative model will be employed, such as the Van Elteren test.

Between-arm comparisons of continuous variables will be performed using the same methodology as for the primary variable, whereas models may include additional explanatory variables, such as the baseline value of specific outcome variables assessed at study end. Logistic regression will be used for comparisons based on binary variables.

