Furthermore, similar models will be used to compare outcome variables between patients from the two cohorts of randomized patients and no SDB patients. Due to the non-randomized design and the definition of the cohorts, the set of explanatory variables included in these models will be different: AHI will not be included, but other potential confounders, such as age and gender may be. No interim analysis of efficacy endpoints is planned. Primary and secondary efficacy outcomes will be analysed after all randomized patients have completed the study or have left it prematurely. Interim analyses of safety may be performed. The analysis of safety data will use descriptive statistical methods. Deviations from the analyses outlined in this section and in the statistical analysis plan will be listed and justified in the Clinical Study Report. No imputation of missing variables will be employed in the primary comparative analysis of efficacy parameters in the two randomization groups. For supportive analyses, imputation strategies considered conservative may be used.

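### The primary ANCOVA is a complete-case analysis of randomised patients with a visit-6 MRI; it guarantees no prognostic covariates and makes no missing-data sensitivity analysis mandatory

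*Protocol article*

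**What the plan says.** All points are from the protocol article.

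- **Outcome** (Primary outcome section). Infarct volumes "are assessed at visit 1 and visit 6", on DWI at the first visit and T2w at the second. "Change of lesion volume from visit 1 to visit 6 is compared between the treatment groups".
- **Timing of the first scan** (Second step of screening). Eligibility for randomisation uses "the lesion diameter confirmed on the MRI at day 1", so the visit-6 scan is the one likely to be missing.
- **Population** (Statistical analysis). The full analysis set holds every enrolled patient and is primary for the randomised comparison. "In line with the intent-to-treat principle, randomized patients will be analysed according to the treatment group assigned at randomization".
- **Model** (Statistical analysis). An ANCOVA adjusted at least for the randomisation strata, which the Randomization section gives as centre and AHI below or from 45/h. Van Elteren is named as a fallback if model conditions fail. Baseline values are mentioned as possible extra covariates for the other continuous variables.
- **Missing data** (Statistical analysis). "No imputation of missing variables will be employed in the primary comparative analysis of efficacy parameters in the two randomization groups". Beyond the main comparison the provision is optional and names no method: "imputation strategies considered conservative may be used".
- **Death** (Assessment of stroke severity and clinical outcome). It counts in a secondary outcome, "a composite endpoint of death from any cause" and several vascular events. No rule is shown for a death before visit 6 in the primary analysis.

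**The concern.** The stated population is everyone randomised, but the analysis that results covers only those with a day-90 scan. Patients who die, withdraw consent or miss that scan might differ from the rest in lesion size or growth. The treatment is open-label without sham, and the Discussion expects compliance of only about 50%, so different loss in the two arms is plausible. If both conditions hold, the primary contrast is no longer protected by randomisation.

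Covariates could reduce this problem, but the two that are guaranteed describe the site and the severity of the breathing disorder, not the severity of the stroke. The supportive analyses are optional, and conservative has no settled meaning here. A carried-forward value, for example, would equate a DWI volume with a T2w volume, and a zero difference between two sequences is not the same as no growth. The article does not propose that particular method, but its wording would allow it.

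**Working it through.** **1. Who enters the primary model.** The outcome is one change value per patient, formed from two volumes. No intermediate volume is planned for it, and imputation is ruled out. A patient without a visit-6 volume therefore has no outcome and contributes nothing to the ANCOVA. The article does not say this outright, but it follows from these rules.

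**2. The article's own power figure.** Inputs from Power calculation and sample size: 134 randomised 1:1 (67 per arm), d = 0.49, SD 20 cm³, two-sided 5% t test. The noncentral t distribution gives 80.4% power, which agrees with the stated minimum of 80%. The detectable difference at 80% power is 0.4876 × 20 = 9.75 cm³, in line with the stated 10 cm³ or so. Both figures require all 134 patients to supply a visit-6 volume; no allowance for loss is stated. Under assumed losses of 5%, 10%, 15% and 20%, power at d = 0.49 is 78.3%, 76.1%, 73.6% and 71.0%.

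**3. Bias of the complete-case difference.** Let p be the fraction missing in an arm and D the excess lesion growth (cm³) of missing over observed patients. Then

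full-arm mean = observed mean + p × D.

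For the difference ASV+ minus ASV−, with the same D in both arms,

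bias = (p in ASV− minus p in ASV+) × D.

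The article gives neither p nor D. All values below are assumptions.

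| Loss, ASV+ v ASV− | D = 10 | D = 20 | D = 40 |
|---|---|---|---|
| equal | 0 | 0 | 0 |
| 5% v 10% | 0.5 | 1.0 | 2.0 |
| 5% v 15%, or 10% v 20% | 1.0 | 2.0 | 4.0 |

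The largest entry is 4.0 / 10 = 40% of the target difference. It needs a 10-point gap in loss together with an excess of two SDs (40 / 20).

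**4. Direction.** As tabulated, the controls lose more patients with large growth. The bias is then positive and understates a benefit of ASV. If ASV+ loses more, the sign reverses and the bias favours ASV.

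**5. Limits of the formula.** If D differs between arms, equal loss does not guarantee zero bias: the general form is (p × D in ASV−) minus (p × D in ASV+). The formula also applies only to patients alive at day 90. A patient who has died has no day-90 volume, so the question there is what to estimate, and it needs its own rule.

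**6. What covariates can do.** A complete-case ANCOVA remains valid if missingness depends only on arm and covariates in the model, and the model is adequate. Visit-1 volume and NIHSS at admission and 24 h are already collected. Neither is guaranteed in the primary model.

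**The case against.** Much of the case on the other side stands.

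- Complete-case ANCOVA is a common primary analysis for a single follow-up measurement. The text bars imputation, not every way of dealing with missing data, and its minimum adjustment set leaves room for visit-1 volume and NIHSS.
- The article refers to a separate statistical analysis plan, where imputation models and sensitivity analyses are commonly detailed. What does not depend on that plan is what the article itself fixes: no imputation in the primary comparison, a minimum covariate set of the strata alone, and supportive imputation that is only optional.
- Loss may be small. Visits are planned with patients, reminders are sent and transport is arranged. Data collection continues after ASV is stopped and ends only if consent is withdrawn. Coma, unstable or life-threatening conditions and significant heart failure are excluded. The composite containing death runs to the one-year contact, so it gives no death rate by day 90.

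A reader might infer that the plan contradicts intention-to-treat. It does not: the article ties that principle to the statement that "randomized patients will be analysed according to the treatment group assigned at randomization", which concerns allocation and does not promise an outcome value for everyone.

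A reader might also infer that multiple imputation in all randomised patients should be primary. That would impute day-90 volumes for the dead, and giving the same patients the worst rank would be a different estimand. Choosing between these is a design trade-off, not the correction of an error.

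**Conclusion.** The concern holds in a limited form. By its own rules the primary comparison is a complete-case analysis of randomised patients with a visit-6 MRI. It can be biased if loss or death before day 90 differs between arms and is related to lesion size or growth. The guaranteed covariates give little protection, and nothing in the article requires an analysis that would show the problem.

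The illustrative range is 0 to 4 cm³ in either direction, against a target of about 10 cm³. It rests wholly on assumed loss rates and an assumed excess growth taken as equal in both arms. Bias is zero when loss and excess growth both match between arms. A reader might take the upper end as an expected bias of up to 40% of the target effect. The article gives no attrition or death rate by day 90, so it does not support that, or any claim that the result will be biased.

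**What to change.** 1. **Primary analysis.** Keep the complete-case ANCOVA, but require visit-1 DWI volume and baseline NIHSS as covariates alongside the randomisation strata. The analysis is then valid when missingness depends on them, and precision should improve.
2. **Sensitivity analyses.** Replace the optional supportive imputation with two mandatory, pre-specified analyses. (a) For survivors without a visit-6 MRI: multiple imputation by arm, with a delta-adjusted tipping point. NIHSS at visit 4 can inform the imputation model, but it is measured after randomisation and should stay out of the ANCOVA. (b) Separately, for deaths before visit 6: a stratified rank analysis by the Van Elteren test, already named in the article, with deaths given the worst rank. State how survivors without a scan enter (b), and that (a) and (b) answer different questions.
3. **Reporting.** Give missing visit-6 MRI by arm and reason, and describe the primary result as applying to patients with a visit-6 scan.

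The cost is some wording, a little programming and a few more sensitivity results to report. No new data are needed. The rules should be fixed before the randomised comparison is run.

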### Power calculation and sample size

Based on feasibility considerations, approximately 134 patients are expected to be randomized in a 1:1 proportion into the group with ASV treatment and without ASV treatment (SDB ASV+ and SDB ASV-). Based on a two-sided *t* test at the 5% significance level, this sample size will provide at least 80% power to detect an effect size (Cohen’s d) of 0.49 for the between-group difference in primary outcome (difference in infarct size from visit 1 (day 1) to visit 6 (day 90)). Based on preliminary investigations in a similar patient pool, the standard deviation is assumed to be 20 cm^3^ (unpublished data), so that the detectable effect size corresponds to a between-arm difference of approximately 10 cm^3^. In secondary analyses, the outcomes will be compared in patients with and without SDB: the detectable difference is expected to be approximately 10 cm^3^ also for this analysis. Calculations were performed using the statistical software package R (https://www.r-project.org/) [39]. These differences are considered meaningful from a clinical point of view.

Based on these considerations, the planned sample size is considered adequate to address the main study objective.

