### Randomization

Random allocation of patients with significant SDB (*n* ~ 134) (AHI > 20/h) in a 1:1 ratio to the two treatment arms is performed using a list with permuted blocks and stratified for the study centre and baseline AHI (AHI < or ≥ 45/h assessed by respiratory polygraphy in the screening night, visit 0). The trial statistician generated the randomization list. Study physicians randomize patients using the electronic data capturing system after obtaining the informed consent and evaluating all exclusion and inclusion criteria. No study personnel, except the trial statistician, has access to the randomization list until completion of the trial.

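### The claim of at least 80% power at d = 0.49 is computed on all 134 randomised patients and leaves room for only one missing visit-6 MRI

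*Protocol article*

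**What the plan says.** All references are to the Protocol article.

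- *Power calculation and sample size* starts from feasibility: "approximately 134 patients are expected to be randomized in a 1:1 proportion". The calculation is for a two-sided comparison of means ("test at the 5% significance level"), and its claim is that "this sample size will provide at least 80% power to detect an effect size". The value of Cohen's d is given as one "of 0.49 for the between-group difference in primary outcome". On variability the section says "the standard deviation is assumed to be 20 cm^3^ (unpublished data", the bracket naming the source of the value. Multiplying the two, it reports that "the detectable effect size corresponds to a between-arm difference of approximately 10 cm^3". It gives no loss rate and no evaluable number.
- *Randomization* confirms allocation "in a 1:1 ratio to the two treatment arms", hence 67 per arm.
- *Assessment of outcomes, primary outcome* defines the endpoint as the change from infarct volume on DWI at visit 1 to infarct volume on T2w MRI at visit 6.
- *Statistical analysis* times the efficacy analysis for when every randomised patient has either finished or left early. On missing data it says: "No imputation of missing variables will be employed in the primary comparative analysis of efficacy parameters". Imputation is kept for supportive analyses.

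**The concern.** The power statement uses the number randomised as if it were the number analysed. A patient without a visit-6 scan has no value for the primary outcome. Because nothing is imputed in the primary comparison, that patient drops out of it, whatever the analysis set is called.

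These are acute stroke patients followed for three months. The article itself provides for death (part of the secondary composite endpoint), withdrawal of consent (which ends data collection) and early leaving. A power figure that tolerates almost no loss is therefore a figure the trial is unlikely to have.

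What is at stake is how the result is read. The section concludes that the sample size is adequate for the main objective, and a null result would be judged against the stated power and detectable difference.

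**Working it through.** **Inputs from the article.** Two-sided α = 0.05; d = 0.49; SD = 20 cm³; 134 randomised 1:1, so n = 67 per arm; unadjusted two-sample t test.

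**Input not in the article.** The share of randomised patients without a visit-6 MRI. It is assumed here to be 5%, 10%, 15% or 20%, equal in both arms.

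**Formula.** Power = P(|T′| > t₀.₉₇₅), where T′ is noncentral t with 2n − 2 degrees of freedom and noncentrality d·√(n/2).

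**Step 1: reproduce the stated figure.** With n = 67 the noncentrality is 0.49 × √33.5 = 2.84, and the power is 80.4%. The smallest d detectable with 80% power is 0.488, and 0.488 × 20 = 9.8 cm³. The article's figure is reproduced, on condition that all 134 are analysed.

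**Step 2: how much loss it tolerates.** Solving for 80% power at d = 0.49 gives n = 66.35, so 67 per arm.

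| Evaluable | Split | Power at d = 0.49 |
|---|---|---|
| 134 | 67/67 | 80.4% |
| 133 | 67/66 | 80.1% |
| 132 | 66/66 | 79.8% |

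One missing scan is tolerable; the second takes power below 80%. So 134 contains no allowance for loss: it is the smallest balanced total that reaches 80% at the stated d.

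**Step 3: apply assumed losses.** Evaluable n per arm = 67 × (1 − loss). The detectable difference is 20 cm³ times the d that gives 80% power at that n.

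| Assumed loss | n per arm | Total | Power at d = 0.49 | d for 80% power | Difference |
|---|---|---|---|---|---|
| 0% | 67.0 | 134 | 80.4% | 0.488 | 9.8 cm³ |
| 5% | 63.7 | 127 | 78.3% | 0.500 | 10.0 cm³ |
| 10% | 60.3 | 121 | 76.1% | 0.514 | 10.3 cm³ |
| 15% | 57.0 | 114 | 73.6% | 0.530 | 10.6 cm³ |
| 20% | 53.6 | 107 | 71.0% | 0.546 | 10.9 cm³ |

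**Step 4: sensitivity to rounding of the effect.** Taking the rounded 10 cm³ literally gives d = 10/20 = 0.50. Then 128 evaluable patients still give 80.1%, so six losses (6/134 = 4.5%) are tolerable. At 10% loss power is 77.7%.

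**Step 5: sensitivity to covariate adjustment.** If the covariates in the planned ANCOVA correlate r with the outcome, d becomes 0.49/√(1 − r²). With r = 0.3, power at 10% loss is 79.9%. With r = 0.4, power at 15% loss is 80.7%. Both values of r are assumptions; the article gives none.

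**The case against.** The strongest reply is that little changes in practice.

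- **The effect on the detectable difference is small.** At 10% loss it moves from 9.8 to 10.3 cm³, which an approximate figure of 10 still covers. The SD comes from unpublished data, and an SD 5% higher would do about the same: 0.488 × 21 = 10.2 cm³. This stands, and it limits the weight of the point. It does not rescue the words *at least 80%* at d = 0.49.
- **The two-patient threshold is a knife edge.** It depends on a d rounded to two decimals and an approximate N, and 79.8% is not meaningfully different from 80%. This also stands. The threshold shows that no allowance was made; it does not measure the damage.
- **Feasibility fixed N.** No inflation step was skipped in deriving it. True, and this is why the remedy concerns the statement and not recruitment.
- **ANCOVA may recover precision.** It may, as step 5 shows. But the power statement rests on a plain t test and claims no gain, and only centre and AHI stratum are fixed as covariates.
- **Retention is addressed.** The Screening and recruitment section describes jointly planned visits, reminders and transport, and data collection continues after ASV is stopped. This lowers the likely loss but cannot prevent loss through death or withdrawn consent.
- **The full protocol or SAP may hold an attrition allowance.** Possibly, but the article ties its power figure to the number randomised, and with any allowance inside 134 the figure would not hold.
- **The Discussion already says that 134 may not suffice.** It does, but the reason given is the lack of data on the treatment effect, not missing scans.

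A reader might infer that the sum is wrong, that the trial is underpowered by a known amount, or that it needs more patients. The documents support none of these. The sum is right for 134 evaluable patients, the loss rate is not given, and N was never derived from a power target. Nor does the point require a named imputation model or separate reporting of deaths by arm: supportive imputation is already allowed, and death from any cause is already collected in the composite endpoint.

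**Conclusion.** The point holds with moderate weight. As written, the power statement is true only if at most one of the 134 randomised patients lacks a visit-6 MRI, while the same article foresees early leaving and excludes imputation from the primary comparison.

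The size of the shortfall depends on a loss rate that must be assumed. At 5% loss, power is under two points below 80%, which is negligible. From about 10% it becomes material: 76%, falling to 71% at 20%. These figures assume equal loss in both arms, SD 20 cm³, d = 0.49 and no gain from covariates. That the article states no allowance is certain; how large the shortfall will be is not.

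**What to change.** Keep N at 134. In Power calculation and sample size, state the expected loss rate and the resulting evaluable number, and give power or detectable difference on that number. With 10% as an illustration, to be replaced by the sponsor's own expectation:

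> *Of about 134 randomised patients, 10% are assumed to lack a visit-6 MRI, leaving about 60 evaluable per arm. A two-sided 5% t test then has 80% power for d of about 0.51 (10.3 cm³ with an SD of 20 cm³); power at d = 0.49 is about 76%.*

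If the sponsor expects ANCOVA to offset the loss, the assumed covariate correlation should be stated beside it. The cost is a sentence of wording and a slightly less favourable figure. The design, the analysis and recruitment do not change.
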